### Secondary Aims

The secondary aims were as follows:

To determine whether the topical application of a protease inhibitor in combination with a topical growth factor reduces protease levels in chronic VLUs and DFUsTo determine whether the topical application of a protease inhibitor increases the levels of endogenous growth factors in chronic VLUs and DFUsTo determine whether there is an increase in healing rates at 4 weeks for both chronic VLUs and chronic DFUs treated with a protease inhibitor dressing in combination with topical PDGF as compared with a placeboTo determine the validity of the WOUNDCHEK Protease Status point-of-care test using the gold standard wound fluid assay of total proteaseTo determine whether the changes in protease and growth factor levels are associated with changes in the potential biomarker of wound healing, GMCSFTo pilot a cost diary for a possible subsequent phase 3 randomized controlled trial whereby cost-effectiveness will be evaluated

## Methods

### Trial Design

This is a proof-of-concept study that is a double-blind, randomized controlled trial. This trial has received provisional approval from the Hamilton Integrated Research Ethics Board, project number 2067.

### Planned Interventions

Participants will be randomized to receive a protease inhibitor or a placebo for 4 weeks of the study, in combination with a topical growth factor. All participants will receive just the topical growth factor for 2 weeks to obtain baseline data on growth factor and protease levels in the wound fluid.

The interventions patients will receive are as follows:

All participants will have Regranex gel (Smith & Nephew) containing a recombinant human PDGF for topical administration, applied to their leg or foot ulcers on a weekly basis for 6 weeks. Regranex is a nonsterile, sodium carboxymethylcellulose-based topical gel. Each gram of Regranex gel contains 100 g of rhPDGF-BB. This is applied by measuring a length of gel from a 15 g tube and is applied at a rate of 0.25 cm length of gel per cm^2^ of ulcer area. A maximum of 2 tubes will be used for each patient, and each patient will have his or her own treatment tubes to ensure that the limit of 2 tubes is not exceeded.Participants randomized to receive the protease inhibitor will receive Promogran (Johnson & Johnson) cut to the size of the ulcer and applied over the rhPDGF-BB.Participants in the placebo arm will receive Aquacel (ConvaTec) dressing applied in a similar manner to the Promogran. This dressing is very similar in appearance to Promogran and has no active protease inhibition function.VLU participants will have an absorbent pad and a 4-layer compression bandage system (Profore, Smith & Nephew) applied over the dressings.Diabetic foot ulcer participants will have an absorbent pad fixed with tape applied over the dressings.

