### Frequency and Duration of Follow-Up

Patients will be followed up 3 times in a week by a research clinical nurse for the treatment and by a blinded research nurse for outcome measurements (Table 1). The first visit could take up to 1.5 hours as wound fluid collection can be slow. The second visit would be scheduled within a 24-hour period and could take up to 1.5 hours for wound fluid collection. This visit would include the application of the protease inhibitor but not the growth factor. The third visit would require 45 min and it is not measurement visit. Table 1 contains the treatments and measurements at each visit for the each of the treatment weeks. There will be one final visit at the end of the last week of treatment.

At the first follow-up visit each week, the following will be performed:

The wound dressing will be taken down and the wound cleansed.The surface area of the wound will be traced and the area will be measured using the Visitrak device (Smith & Nephew).A photograph of the wound will be taken using a standardized protocol.The amount of rhPDGF-BB to be applied for that week will be calculated based on the ulcer size.A swab of the fluid on the surface of the wound will be taken using the WOUNDCHEK system to assess for elevated protease activity.A sample of wound fluid will be collected using a standardized methodology.The rhPDGF-BB will be applied to the wounds.The protease inhibitor dressing or the placebo will be applied.The secondary dressings will be applied.

At the second follow-up visit each week, the following will be performed:

Wound fluid will be collected.No measurements will be done; wound photography will be taken.The rhPDGF-BB will be applied to the wounds.The protease inhibitor dressing or the placebo will be applied.The secondary dressings will be applied.

At the third follow-up visit in the same week, the following will be performed:

No measurements, wound photography or fluid collection.The rhPDGF-BB will be applied to the wounds.The protease inhibitor dressing or the placebo will be applied.Secondary dressings will be applied.

**Table 1 table1:** Treatments and measurements at each study visit.

Day	Growth factor application	Protease inhibitor application	Wound fluid collection	Point of Careswab for total protease activity (WOUNDCHEK)
1	x	x	x	x
2	x	x	x	x
5	x	x		x

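### Gel rule, 64 cm² size limit, two-tube cap and application schedule are not shown to be compatible, and the article gives three different application frequencies

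*Protocol article*

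**What the plan says.** Planned Interventions gives every participant PDGF gel, "applied to their leg or foot ulcers on a weekly basis for 6 weeks". Tubes hold 15 g each. The dose follows ulcer size: "applied at a rate of 0.25 cm length of gel per cm^2^ of ulcer area". The same paragraph sets the limit: "A maximum of 2 tubes will be used for each patient". Individual tubes for each patient are the means of enforcing it. Two of the six weeks are gel only, for baseline data; the randomised dressing is used for four weeks.

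Inclusion and Exclusion Criteria admits ulcers of 1 to 64 cm².

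Frequency and Duration of Follow-Up sets three visits a week: "Patients will be followed up 3 times in a week by a research clinical nurse for the treatment". At the first visit of each week, "The amount of rhPDGF-BB to be applied for that week will be calculated based on the ulcer size". On whether gel is given at each visit, the section disagrees with itself:

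- The narrative says of the second visit: "This visit would include the application of the protease inhibitor but not the growth factor".
- The list for the second visit includes gel, and so does the list for the third: "No measurements, wound photography or fluid collection.The rhPDGF-BB will be applied to the wounds".
- Table 1 marks growth factor on days 1, 2 and 5.

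Randomization Method says that randomised patients get all their allocated treatments throughout the study. The Introduction reports a product-label warning for patients who use three or more tubes.

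**The concern.** The dose is set in centimetres and the cap in tubes, and nothing in the article links the two. The article therefore does not show that the largest eligible ulcer can be treated for six weeks within the cap. The three accounts of frequency change the gel needed by a factor of three.

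This bears on the primary outcome, which is the level of nondegraded PDGF in wound fluid, compared between arms by repeated measures ANOVA. If a patient's gel is used up before week 6, samples taken afterwards contain no recently applied PDGF, whichever dressing is on the wound. They carry little information on whether the protease inhibitor protects applied PDGF, and they pull the arm difference towards zero. The cap also lies just below the tube count named in the label warning, so it cannot be presumed flexible.

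**Working it through.** The article states no total gel requirement, so there is no figure of its own to reproduce beyond the cap: 2 tubes × 15 g = 30 g.

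**Inputs from the article.** Largest area 64 cm²; rate 0.25 cm per cm²; six treatment weeks; cap 30 g. Applications:

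- 6, if the weekly wording in Planned Interventions means once a week;
- 12, if the second visit is left out, as in the follow-up narrative (2 × 6);
- 18, by the visit lists and Table 1 (3 × 6).

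**Input not in the article.** Gel weight w in g/cm. It is treated as an assumption, with values 0.10, 0.15, 0.25 and 0.40.

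**Step 1: gel needed at 64 cm², constant area, rate read as per application.** Length per application = 64 × 0.25 = 16 cm. Total length = 16 × N. Break-even weight = 30 / total length.

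| Applications N | Gel (cm) | Cap holds if w is at most (g/cm) |
|---|---|---|
| 6 | 96 | 30/96 = 0.3125 |
| 12 | 192 | 30/192 = 0.156 |
| 18 | 288 | 30/288 = 0.104 |

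**Step 2: largest ulcer that can receive every application.** Area = 30 / (0.25 × N × w).

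| w (g/cm, assumed) | N = 6 | N = 12 | N = 18 |
|---|---|---|---|
| 0.10 | 200 cm² | 100 cm² | 66.7 cm² |
| 0.15 | 133 cm² | 66.7 cm² | 44.4 cm² |
| 0.25 | 80 cm² | 40 cm² | 26.7 cm² |
| 0.40 | 50 cm² | 25 cm² | 16.7 cm² |

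Values below 64 cm² mean that some eligible ulcers cannot be fully treated within the cap.

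**Step 3: when the gel runs out (64 cm², 18 applications).** Weeks covered = 30 / (3 × 16 × w) = 0.625 / w. This gives 6.25 weeks at 0.10 (enough), 4.17 at 0.15, 2.5 at 0.25 and 1.56 at 0.40. Supply ends in the four randomised-dressing weeks (treatment weeks 3 to 6) only if w lies between 30/288 = 0.104 and 30/96 = 0.3125 g/cm. Above 0.3125 it ends in the gel-only weeks; below 0.104 it lasts.

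**Step 4: allowing for healing.** The dose is recalculated weekly. Take 40% and 50% linear shrinkage over four weeks, the thresholds in Outcome Measures.

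- Shrinkage only in the dressing weeks. At 40% the weekly areas are 64, 64, 64, 57.6, 51.2 and 44.8, sum 345.6. Gel = 345.6 × 0.25 × 3 = 259.2 cm; break-even 30/259.2 = 0.116 g/cm. At 50% the sum is 336, gel 252 cm, break-even 0.119 g/cm.
- Shrinkage at the same rate from treatment week 1. At 40% the sum is 288, gel 216 cm, break-even 0.139 g/cm. At 50% the sum is 264, gel 198 cm, break-even 0.152 g/cm.

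Healing eases the constraint but does not remove it at 18 applications.

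**The case against.** A reader might infer that the limits cannot all be met. The article does not support that. Impossibility needs the weight of gel per cm, which is not given; at 0.10 g/cm a 64 cm² ulcer takes 28.8 g over 18 applications and stays within the cap. Nor is there one schedule to test against. With once-weekly use the rules fit a 64 cm² ulcer up to 0.3125 g/cm. The follow-up section also speaks of an amount for the week, so the rate may be a weekly quantity. The total is then 96 cm however many visits share it. All of this stands.

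A reader might also infer that the gel runs out in the randomised-dressing weeks. At 18 applications and 64 cm² that holds only between 0.104 and 0.3125 g/cm.

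A third tempting reading is that the primary comparison is biased because faster-healing ulcers use less gel and stay under the cap longer. The mechanism is possible, but the article gives no ulcer-size distribution and nothing from which a difference in exposure between arms could be sized. Nor does it say that a patient who reaches the cap continues to be sampled.

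Finally, a condensed article may leave the conversion and the handling of exhausted supply to the full protocol. That is fair, and their absence alone would not be a finding. It does not excuse conflicting statements of frequency within the article, on which the adequacy of the cap depends.

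**Conclusion.** The point holds as a conditional inconsistency. Planned Interventions and the two accounts in the follow-up section disagree on how often gel is applied. Settling that alone does not settle the cap: each per-application reading has a break-even weight (0.31, 0.16 or 0.10 g/cm) that the article gives no means of checking, and the weekly-quantity reading shares the 0.31 limit.

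On the three-visit reading, the largest fully treatable ulcer falls from about 67 to 17 cm² as assumed gel weight rises from 0.10 to 0.40 g/cm, so over most of that range larger eligible ulcers would exhaust their supply before week 6. These figures rest on constant area and a per-application rate.

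The likely harm is dilution of the primary comparison. Its size cannot be given, because the share of large ulcers is unknown. Differential exposure by arm is possible but not quantified. The matter deserves correction before enrolment because it touches both the primary measurement and the tube limit.

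**What to change.** Reconcile the application frequency in Planned Interventions with the narrative, visit lists and Table 1 in Frequency and Duration of Follow-Up. Then check the result against the size range, the gel rule and the two-tube cap. State whether the rate is per application or per week, give the cm-to-gram conversion, and show the calculation for the largest eligible ulcer. Which of these elements should change is for the investigators; this review takes no position.

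Log the gel used at each application and report by arm how many patients reach the cap, and when.

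Keep all randomised patients and all scheduled samples in the primary PDGF analysis. An analysis limited to weeks in which gel was applied may be added as a sensitivity analysis only. Reaching the cap happens after randomisation and may depend on arm through healing, so restricting the primary comparison to those weeks could itself introduce bias.

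The cost is protocol wording and a dispensing log, since tubes are already assigned to individual patients. If the investigators choose to narrow the size range, recruitment may slow slightly.

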### Randomization Method

Randomization will occur after the first week in which the participant’s compliance with optimal standard therapy is assessed. If the participant is not compliant at this point, he or she will not be randomized into the study. The research coordinator will randomly assign eligible participants using a computer-generated randomization tool. Following eligibility screening by the research coordinator, the system will generate a unique number. The research coordinator then telephones the treatment nursing staff and reports the number. In turn, treatment research nurses refer to a manual of unique numbers generated by an independent biostatistician before study activation to determine the study intervention allocated to the randomized patient. The randomization schedule will be stratified by wound type (VLU or DFU) in variable blocks of 4 and 6. Randomized patients will receive all treatments during the study period according to the intervention they were allocated. The patients, study investigators, research coordinator, laboratory technologists, and assessing research nurses will be blinded to the treatment allocation. Only the treating team members are not blinded.

### Protecting Against Bias

The researchers assessing the protease, growth factor, and biomarker levels in the wound fluid will be blinded to the treatment group, as will the researcher who performs the measurements on the wounds. A dressing similar in appearance to Promogran will be used in the control group so that the participants will also be blinded.

### Inclusion and Exclusion Criteria

Inclusion criteria were as follows:

Men and women aged ≥18 yearsUlcer size 1-64 cm^2^Ulcer extends through both the epidermis and dermis, with no exposed tendon or boneUlcer duration >3 months and <12 monthsUlcer located between and including the knee and ankleFor VLUs—venous refilling time <25 s on photoplethysmography or abnormal venous insufficiency duplex scanFor DFUs—confirmed type 1 or type 2 diabetes mellitus with a hemoglobin A1C <12%Wounds that have not been treated with Promogran in the previous 4 weeksPatients able to give informed consent

Exclusion criteria were as follows:

Ankle-brachial index <0.8Ulcer with local or systemic signs of infectionPatients who have been previously treated with rhPDGF-BB gelPatients receiving corticosteroids or immune suppressantsHistory of autoimmune diseaseUncontrolled diabetes (baseline hemoglobin A1C >12%)Severe rheumatoid arthritisUncontrolled congestive heart failureMalnutrition (albumin <2.5 g/dL)Unable to adhere to the protocolKnown sensitivities to the wound dressings used in the trialHistory of any previous malignancyPregnant or lactating woman

### Treatment Period

Participants will be in the study for a total of 7 weeks. During the first week, participants will not receive the study treatment. During this week, the participants with VLUs will have a standardized bandaging regimen applied and the DFU participants will have their pressure off-loading optimized. Once they have demonstrated tolerance and compliance for wearing these bandaging, they will continue for 6 weeks of study treatment.

### Frequency and Duration of Follow-Up

Patients will be followed up 3 times in a week by a research clinical nurse for the treatment and by a blinded research nurse for outcome measurements (Table 1). The first visit could take up to 1.5 hours as wound fluid collection can be slow. The second visit would be scheduled within a 24-hour period and could take up to 1.5 hours for wound fluid collection. This visit would include the application of the protease inhibitor but not the growth factor. The third visit would require 45 min and it is not measurement visit. Table 1 contains the treatments and measurements at each visit for the each of the treatment weeks. There will be one final visit at the end of the last week of treatment.

At the first follow-up visit each week, the following will be performed:

The wound dressing will be taken down and the wound cleansed.The surface area of the wound will be traced and the area will be measured using the Visitrak device (Smith & Nephew).A photograph of the wound will be taken using a standardized protocol.The amount of rhPDGF-BB to be applied for that week will be calculated based on the ulcer size.A swab of the fluid on the surface of the wound will be taken using the WOUNDCHEK system to assess for elevated protease activity.A sample of wound fluid will be collected using a standardized methodology.The rhPDGF-BB will be applied to the wounds.The protease inhibitor dressing or the placebo will be applied.The secondary dressings will be applied.

At the second follow-up visit each week, the following will be performed:

Wound fluid will be collected.No measurements will be done; wound photography will be taken.The rhPDGF-BB will be applied to the wounds.The protease inhibitor dressing or the placebo will be applied.The secondary dressings will be applied.

At the third follow-up visit in the same week, the following will be performed:

No measurements, wound photography or fluid collection.The rhPDGF-BB will be applied to the wounds.The protease inhibitor dressing or the placebo will be applied.Secondary dressings will be applied.

**Table 1 table1:** Treatments and measurements at each study visit.

Day	Growth factor application	Protease inhibitor application	Wound fluid collection	Point of Careswab for total protease activity (WOUNDCHEK)
1	x	x	x	x
2	x	x	x	x
5	x	x		x

### Outcome Measures

Primary outcome:

The difference in levels of nondegraded PDGF in CWF from the treatment and placebo treatment groups

Secondary outcomes:

The difference in levels of total protease and individual proteases in CWF from the treatment and placebo treatment groups as determined by enzyme-linked immunosorbent assay (ELISA) assayThe difference in levels of endogenous growth factors in CWF from the treatment and placebo treatment groups as determined by ELISA assayPercentage reduction in size of ulcers after 1 month of therapy and the proportion of VLU and DFU that are in a healing trajectory. In VLU, a wound area reduction of 40% within 4 weeks is predictive of healing at 12 weeks [67], and in DFUs, a wound area reduction of greater than 50% in 4 weeks is predictive of healing at 12 weeks [68]The presence of elevated total protease activity using WOUNDCHEK and the change with timeThe presence of a healing or nonhealing status as measured by GMCSF levels in CWF and the change with time as measured by ELISA assayThe completeness, ease of use, literacy, and timeliness of completing the pilot cost diary from a societal perspective. Both medical staff and participants will complete cost diaries

### Measurement of Outcomes at Follow-Up Visits

At the first follow-up visit each week, the following will be performed:

The surface area of the wound will be traced and the area will be measured using the Visitrak device (Smith & Nephew).A photograph of the wound will be taken using a standardized protocol.A swab of the fluid on the surface of the wound will be taken using the WOUNDCHEK system to assess for elevated protease activity. The swabs will be stored for subsequent analysis of actual protease levels.A sample of wound fluid will be collected from the chronic wounds by covering the wound with a transparent occlusive dressing (Opsite, Smith & Nephew, Hull, UK) for approximately 1 hour. Fluid that has accumulated will then be aspirated and stored at −80°C. The wound fluid samples will be aliquoted into 20 ul samples and will be stored at −80°C. At the completion of the study, the samples will be analyzed using Quantibody analysis to measure the levels of proteases and nondegraded growth factors in the wound fluid, and a Western blot will be performed to assess rhPDGF-BB degradation. All of these samples will be assayed at the end of the study.

At the second visit in the same week, the following will be performed:

A sample of wound fluid will be collected.A swab of the fluid on the surface of the wound will be taken using the WOUNDCHEK system to assess for elevated protease activity.

At the third follow-up visit in the same week, the following will be performed:

Swab of the fluid on the surface of the wound will be taken using the WOUNDCHEK system to assess for elevated protease activity.The cost diary for that week will be completed.

### Health Services Issues

As this is a proof-of-concept study of the biochemical efficacy of the therapy, no health service evaluations will be undertaken; however, a cost diary from a societal perspective will be validated in preparation for a future study.

### Sample Size

One small study has assessed the levels of proteases in CWF from VLU after the application of Promogran [43]. In that study, the reduction in elastase after 5 days was approximately 80%, and the reduction in MMP-9 was approximately 45%. There are no data on the degradation of rhPDGF-BB that is applied topically to VLU or DFU. For the sample size analysis, a modest reduction in protease levels of 25% was estimated. Due to the variability of factors, an SD of 35% of the value for the control levels was used. Using a power of 80% and a 5% level of significance, the calculated sample size was 31 in each group. Due to possible nonadherence with the study and collection of samples, the number of participants to be recruited is 40 in each group.

### Planned Recruitment Rate

Patients will be approached and recruited by the research coordinator after being identified in the clinic by the participating physicians. The study will be conducted over 3 years. The first 3 months requires study preparation including intensive protocol training to ensure reliability. A number of protocols such as wound fluid collection are not typical wound care procedures. On the basis of previous studies from this laboratory, recruitment will need 2 years, given the average of 3.5 participants recruited per month. The last 3 months will include conducting the assay analysis and data analysis and disseminating the results.

### Compliance

On the basis of previous studies from this laboratory, compliance is a risk, given the complexity of the participants’ chronic wound, comorbidities, and tolerance for either compression bandaging or pressure off-loading. Compliance will be assessed on the participants’ second visit by noting if they are wearing their prescribed compression bandaging or pressure off-loading device. If they are not complying with standard therapy, the participants will not enter the treatment segment of the study. The need to attend the study clinic 3 times a week for 6 weeks is demanding and risks noncompliance; however, these visits replace the need for the participants to attend their regular clinic to have their dressings changed.

